### Study procedures

All patients randomized to group A will undergo a dangling protocol. In Table 2 this dangling protocol is further specified. The flap will be wrapped during the dangling procedure. After 5–7 weeks, 2.5–3.5 months, and 5–7 months, the patients will be seen at the outpatient clinic to evaluate complications. Photographs of the flap will be taken on POD 6 or 7 and at all planned follow-up visits. These photos will be used in a sample test to check whether the estimated percentage partial flap necrosis and skin graft take was estimated correctly.

**Table 2 Tab2:** Dangling protocol for patients in group A in the free flap group

Postoperative day	Duration of dangling 3 times a day
7	5 min
8	10 min
9	20 min
10	30 min
11	45 min
12	60 min
13	Unlimited

Patients in group B are allowed to dangle for an unlimited time starting on POD 7. Patients in group B are allowed to go home (if the wound status and further co-morbidities allow) and will be seen at the outpatient office between PODs 12 and 15 (depending on the weekends) and after 5–7 weeks, 2.5–3.5 months, and 5–7 months. From POD 7 until POD 14 patients will wear a step counter and will keep track of the time they spent standing or sitting with their leg down. The flap will be wrapped starting on POD 7. During the outpatient office visits the complications will be evaluated.

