Jokuszies et al. [4] and Neubert et al. [5] performed the only two known randomized controlled trials in this patient group. They compared an early start of the dangling protocol on POD 3 to the more standard starting point on POD 7. Both studies showed that the combined wrapping and dangling procedure can safely be started at POD 3. It must be noted that the patients included in these studies were for the most part the same group of patients. Furthermore, the numbers of patients in both studies were small (31 and 49), resulting in an underpowered study [4, 5]. McGhee et al. published a systematic review comparing an early dangling protocol to a late dangling protocol [6]. They found eight relevant articles, including the studies performed by Jokuszies et al. [4] and Neubert et al. [5]. Based on the currently available literature, they concluded that an early dangling protocol can be safely used. A more recent systematic review by Soteropulos et al. came to a similar conclusion [7].

Both systematic reviews are calling for a larger randomized controlled trial. Moreover, whether or not to dangle at all is an intriguing question. We hypothesize that the free flap as a result of flap ingrowth regains its venoarterial response and will develop increased venous outflow over time. We believe that this is independent of a dangling protocol. Therefore, we designed a study protocol for a large multicenter randomized controlled trial, which we present in this article.

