## Methods/design

### Trial design

The study is taking place at three Dutch hospitals: University Medical Center (UMC) Utrecht, Erasmus University Medical Center (Erasmus MC) Rotterdam, and UMC Groningen. A dangling protocol is the current standard of care in these hospitals. Patients are randomly assigned by a computer program to group A or B. Patients in group A start a dangling protocol on POD 7. Patients in group B can mobilize without limitations starting on POD 7 and are discharged from the hospital when possible. All patients will be seen on POD 12–15, after 5–7 weeks, 2.5–3.5 months, and 5–7 months at the ward or the outpatient clinic. During these visits the complications will be evaluated. The study phases and data collection time points are shown in Fig. 1. The Standard Protocol Items: Recommendations for Interventional Trials (SPIRIT) checklist is provided as Additional file 1.

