### Randomization

Randomization will be performed in Castor EDC, Amsterdam, the Netherlands. This study cannot be blinded. The randomization is stratified per medical center. The coordinating researcher will log in to the computer system and fill out the required information. In case of a re-intervention, the patient will still be included in the study. If the arterial and/or venous anastomosis required a redo, then the day of the performed re-intervention will be POD 0. The study (dangling or no-dangling protocol) will start 7 days after the re-intervention.

In case the patient has a partial or complete flap loss and a secondary free flap transplantation is indicated, the patient will not be re-invited to join the study for randomization after the secondary free flap.

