### Statistical analysis

As the primary hypothesis we will calculate the absolute risk differences in incidence of partial flap loss (major and minor combined) between groups. If the upper limit of the 95% CI falls within 12%, we regard this as a non-inferiority difference.

The secondary hypotheses will be tested for superiority: absolute risk difference for one or more major complications and 95% CI, and linear regression for length of stay, physical function, and blood tests.

We will perform an intention-to-treat analysis. However, since investigators can decide to withdraw a subject from the study for life-threatening medical reasons (see the subsequent section on Recruitment, consent, and withdrawal), we will perform an additional per protocol analysis and compare baseline characteristics of patients withdrawn and patients lost to follow-up. We will use multiple imputation to account for missing variables.

We will perform an interim analysis when 40 patients are randomized. If we find a significant difference through Fisher’s exact test in patients having one or more major or minor complications, we will terminate the trial. Based on previous studies, we will test our final non-inferiority hypothesis without alpha adjustment for the superiority tested interim analysis.

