### Study data management, oversight, and publication

Data will be handled confidentially. Data will be collected in the electronic patient file by the local researcher and subsequently registered in Castor EDC, Amsterdam, the Netherlands. Patients will be anonymized. The handling of personal data will be performed in compliance with the Dutch Personal Data Protection Act and in compliance with Good Clinical Practice guidelines. Data will be kept for 15 years. Informed consent from study participants will be recorded at every hospital in the electronic patient file, and signed paper forms will be securely locked away within the hospital where the patient is undergoing treatment.

The study is monitored by an independent monitoring company (Julius Clinical, Zeist, the Netherlands) according to a detailed monitoring plan. Insurance is provided for all participants in accordance with Dutch legislation. The results of this study will be submitted to peer-reviewed journals.

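### The blanket statement that the trial cannot be blinded overlooks the planned flap photographs, which could be read with the arm hidden to test a primary outcome judged at open-label visits

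*Protocol article*

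**What the plan says.** **Blinding.** The Randomization section says "This study cannot be blinded" and makes no exception for outcome assessment.

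**Assessment.** The Trial design section lists ward or outpatient contacts at POD 12-15, 5-7 weeks, 2.5-3.5 months and 5-7 months, and adds: "During these visits the complications will be evaluated". No assessor is named. Under Study data management, oversight, and publication: "Data will be collected in the electronic patient file by the local researcher".

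**Outcome.** The primary analysis concerns "absolute risk differences in incidence of partial flap loss (major and minor combined) between groups" (Statistical analysis). The Study parameters section separates minor from major partial loss only by whether a second free flap is needed. It sets no smallest percentage that counts as a loss.

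**Photographs.** Under Study procedures: "Photographs of the flap will be taken on POD 6 or 7 and at all planned follow-up visits". Their stated use is: "These photos will be used in a sample test to check whether the estimated percentage partial flap necrosis", and likewise skin graft take, was judged correctly.

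**Expectation.** On the recovery of flap outflow over time, the Background says "We believe that this is independent of a dangling protocol".

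**Limitations.** The consequence drawn there from the lack of blinding is that group B patients might dangle on their own initiative. Bias in judging the outcome is not discussed.

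**The concern.** Patients and treating staff cannot be kept unaware of whether dangling takes place. A reader of a photograph with identity and arm removed can be. The statement in the Randomization section is therefore wider than the facts require, and the article already plans both the images and a reading task.

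This matters because of the kind of outcome. Minor partial loss with no lower limit on its extent is a matter of judgement, and someone who knows the arm may judge it differently in the two groups. In a non-inferiority trial, under-calling losses in the no-dangling arm pushes towards a false claim of non-inferiority. Over-calling them there pushes towards failing to show it when it is true. The investigators' stated expectation suggests the first, while caution about leaving out standard care could produce the second.

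**Working it through.** **Inputs.** Control rate 6%, margin 12 percentage points, 80% power, two-sided 95% CI, 5% loss to follow-up, total 130 (Sample size calculation). Non-inferiority is claimed if the upper limit of the 95% CI lies within 12% (Statistical analysis). Assumed: 1:1 allocation, and the misreading rates used in step 4.

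**1. The plan's own figure.** n per arm = 2p(1 − p)(z₀.₉₇₅ + z₀.₈₀)²/δ² = 2 × 0.06 × 0.94 × (1.960 + 0.842)²/0.12² = 61.5, so 62 per arm and 124 in total. Without rounding per arm, the total after 5% loss is 129.4, i.e. 130; with rounding it is 124/0.95 = 130.5, i.e. 131. The stated 130 reproduces, so the sample size is not at issue. The rest uses 62 evaluable patients per arm.

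**2. How few flaps decide the result.** Take 4 events in group A (4/62 = 6.5%). The Wald upper limit is p_B − p_A + 1.96 × √[p_A(1 − p_A)/62 + p_B(1 − p_B)/62].
- 5 events in B: upper limit 10.7%, non-inferiority claimed.
- 6 events in B: upper limit 12.8%, not claimed.

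The largest group B count that still passes is 5 (Wald), 5 (Newcombe) or 4 (Miettinen-Nurminen).

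**3. Method for the error rates.** For each pair of event counts (a, b), multiply the binomial probabilities Bin(62, p_A) and Bin(62, p_B), and sum over the pairs whose upper limit is below 12%. If a share s of true group B losses is recorded, the recorded rate in B is s × 18%. For s = 0.8 that is 14.4%, or about 9 flaps where 0.18 × 62 ≈ 11 are truly affected.

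**4. Results.**

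| True rates (A v B) | Misreading (assumed) | Wald | Newcombe | Miettinen-Nurminen |
|---|---|---|---|---|
| *Chance of a false non-inferiority claim* | | | | |
| 6% v 18% | none | 3.6% | 2.5% | 2.2% |
| 6% v 18% | 1 in 5 missed, B only | 12.9% | 9.3% | 8.2% |
| 6% v 18% | 3 in 10 missed, B only | 22.1% | 16.4% | 14.5% |
| *Power* | | | | |
| 6% v 6% | none | 82% | 72% | 69% |
| 6% v 6% | B recorded as 9% | 52% | 42% | 38% |

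The last row is 0.03 × 62 ≈ 2 extra flaps called in group B.

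**5. What masking cannot cure.** If 1 in 5 losses is missed in both arms alike (4.8% v 14.4% recorded), false non-inferiority is 9.7% (Wald) or 6.3% (Newcombe). This comes from insensitive reading, not from knowing the arm.

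**The case against.** The strongest reply is that the article condenses a fuller protocol (version 7.0) that is not shown. A reader might infer that the photograph check is unmasked and has no bearing on the primary result. The article says neither; it is silent on both, and the full protocol may settle them. That the assessors know the arm is likewise inferred, from the blanket statement on blinding and from assessment at clinical visits. What the text does fix is the blanket statement and a check limited to a sample.

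The calculations are also illustrative. They place the truth exactly at the margin and put the error in one arm. Loss needing a second free flap is unlikely to be overlooked, so missing 1 in 5 of all losses implies a higher miss rate among minor ones. Each flap is also seen at four follow-up visits. These points limit how large a bias is plausible, but they do not remove the sensitivity to one or two flaps.

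A reader might also conclude that masked photographs should replace the clinical assessment as the primary outcome. The article does not support going that far. A photograph may show depth of loss less well than an examination, so that would be a trade-off and not a plain correction. Nor would it be enough to add masked reading only at visits where a loss had been flagged, because a loss under-called at the visit would never reach the masked reader.

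**Conclusion.** The point holds in a limited form. The statement on blinding is too broad, and a judgement-based primary outcome is left to open-label assessment although suitable images and a reading task are already planned. Under the assumed error of 1 in 5 group B losses missed, false non-inferiority at the margin rises from about 2-4% to 8-13%. Under the assumed 3-point over-call in group B, power falls from 69-82% to 38-52%. Both rest on 62 evaluable patients per arm and cover three common interval methods.

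The documents give no size or direction of bias, so these figures show how sensitive the result is; they do not predict what will happen. It would go too far to say that the trial is biased towards non-inferiority. The change is worth making because it is cheap and the result turns on so few flaps.

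**What to change.** 1. In Randomization, limit the statement on blinding to patients and treating staff.
2. In Study procedures, have the planned photograph check done with identity and arm removed, against the same definition of partial loss that is used at the visits.
3. Include every recorded or suspected loss, plus a random sample from both arms of flaps recorded as having no loss. Cover all follow-up visits after POD 7, not only flagged ones. The POD 6 or 7 photograph is taken before or at the start of the intervention, so it serves as a baseline and cannot show an effect.
4. Report agreement between the masked reading and the visit assessment by arm.
5. Repeat the non-inferiority analysis with the masked readings as a prespecified sensitivity analysis. Keep the clinical assessment as primary.

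**Cost.** Wording and some extra reading hours. The ceiling is 130 patients × 4 follow-up visits = 520 photographs if every flap were read, and a sample needs fewer. No new images or visits are needed, nor any reader beyond the one the sample check implies, and the sample size stays at 130. The downsides are that photographs may show depth of loss less well than examination, and that masking does not correct under-calling that is equal in both arms.

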### Point-of-care blood tests

All of the randomized patients in group A at the UMC Utrecht will undergo blood tests. Using a POCT device, a drop of blood from the free flap and from the contralateral “healthy” leg (control group) will be analyzed for blood gases (pO2, pCO2, pH). If the patient has a bilateral leg injury, the drop of blood will be taken from a different body part. This study is designed to get a better insight into the gaseous changes within the free flap during the dangling process. Blood will be taken from the free flap and the contralateral leg at the beginning and at the end of the dangling session. Table 3 illustrates the protocol for the POCT. The goal of these POCT measurements is to present a curve of the gaseous changes during a dangling protocol and to get more insight into the effect of dangling on these blood gases.

**Table 3 Tab3:** Point-of-care testing (POCT) protocol during the dangling protocol

Postoperative day	Before a dangling session	At the end of a dangling session
7	POCT from flap and contralateral leg	POCT from flap
8	POCT from flap and contralateral leg	POCT from flap
9	POCT from flap and contralateral leg	POCT from flap
10	POCT from flap and contralateral leg	POCT from flap
11	POCT from flap and contralateral leg	POCT from flap
12	POCT from flap and contralateral leg	POCT from flap

### Anticoagulant use during the study

The use of coumarins or a novel oral anticoagulant will be preoperatively stopped. If the patient has an indication for “bridging” with a therapeutic dose of low molecular weight heparin (LMWH) due to co-morbidities, this will be done. If bridging is not indicated, the patient will receive a prophylactic dose of LMWH to reduce the risk of deep venous thrombosis or pulmonary embolism, which is standard of care for all patients undergoing surgery in the Netherlands.

Patients who use acetylsalicylic acid will continue this medication. Acetylsalicylic acid will not be started in patients after a free flap, in case the patients did not use this medication before the operation.

### Sample size calculation

Based on the incidence of partial flap necrosis in the meta-analysis by Xiong et al., we performed a power calculation [8]. Because total free flap loss rarely occurs after POD 5, we decided to focus in this study on partial flap loss. Based on a rate of partial flap loss of 6%, we decided that an absolute increase in incidence of 12% would be clinically significant. To detect this non-inferiority margin with 80% power and a two-sided 95% confidence interval (CI) and 5% estimated loss to follow-up, we aim to include 130 patients. Each year about a hundred lower limb reconstructions are performed at our three hospitals, resulting in an inclusion time of 2 years.

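### At 130 patients and a 6% event rate, the stated 80% power and 95% confidence level do not hold together; which one fails depends on the interval, which the article does not name

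*Protocol article*

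**What the plan says.** The Sample size calculation section assumes a 6% rate of partial flap loss and sets the margin: "we decided that an absolute increase in incidence of 12% would be clinically significant". It then states the operating characteristics and the allowance for loss, "To detect this non-inferiority margin with 80% power and a two-sided 95% confidence interval (CI) and 5% estimated loss to follow-up", and concludes "we aim to include 130 patients".

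The Statistical analysis section makes the confidence limit the sole criterion for the primary hypothesis: "If the upper limit of the 95% CI falls within 12%, we regard this as a non-inferiority difference". The effect measure is the absolute risk difference, with major and minor partial flap loss combined. The same section plans an intention-to-treat analysis, with multiple imputation for missing values.

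Neither section names the sample-size formula or the method for the confidence interval.

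**The concern.** Power and confidence level are both explicit claims, so they can be checked against the exact binomial distribution. At a 6% rate and about 62 patients per arm, the expected count is 62 × 0.06 = 3.7 events per arm. Normal approximations for a risk difference are unreliable with so few events, and the simple Wald interval tends to be too short on the side that matters for non-inferiority.

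What is at stake is the meaning of the primary conclusion. If the upper limit comes from an interval that is too short, non-inferiority is declared too often when omitting dangling is worse by the full margin. If it comes from an interval that holds its level, the trial is more likely to end inconclusively than the article tells its readers. The Limitations section already concedes that the 12-point margin is wide and was chosen for feasibility, which leaves little room for extra leniency in the interval.

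**Working it through.** **Inputs.** From the Sample size calculation section: 6% event rate, 12-point absolute margin, two-sided 95% interval (one-sided 2.5% for non-inferiority), 80% power, 5% loss, 130 patients. Implied but not stated: 1:1 allocation, and a true rate of 6% in both arms.

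**Step 1: reproduce the 130.** Unpooled normal (Wald) formula, per arm:

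n = (1.96 + 0.8416)² × 2 × 0.06 × 0.94 / 0.12² = 7.849 × 0.1128 / 0.0144 = 61.5, so 62.

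Total evaluable: 2 × 61.48 = 122.96 unrounded, or 124 rounded. After 5% loss: 122.96 / 0.95 = 129.4, or 124 / 0.95 = 130.5. Both agree with 130.

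Other formulas do not fit the stated inputs:
- Score (Farrington-Manning) formula at one-sided 2.5%: 81 per arm, 162 / 0.95 = 171 randomised.
- Wald at one-sided 5%: 49 per arm, 104 randomised.
- Score formula at one-sided 5%: 63 per arm, 133 randomised. This is close to 130 but contradicts the stated 95% interval.

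**Step 2: exact operating characteristics.** For every pair of event counts (x in group B, y in group A), compute the upper 95% limit for the risk difference and mark the pair as a pass if the limit is below 12%. Sum the product of the two binomial probabilities over the passing pairs. Power uses 6% v 6%; false non-inferiority uses 6% in A and 18% in B, against a nominal 2.5%.

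| Per arm | Interval | Power, 6% v 6% | False non-inferiority, 6% v 18% |
|---|---|---|---|
| 61 | Wald | 79.5% | 3.5% |
| 61 | Newcombe | 69.7% | 2.4% |
| 61 | Miettinen-Nurminen | 67.6% | 2.1% |
| 62 | Wald | 82.1% | 3.6% |
| 62 | Newcombe | 72.1% | 2.5% |
| 62 | Miettinen-Nurminen | 69.1% | 2.2% |
| 62 | Profile likelihood | 75.4% | 2.6% |
| 62 | Agresti-Caffo | 75.9% | 2.6% |
| 65 | Wald | 81.4% | 3.4% |
| 65 | Newcombe | 75.5% | 2.6% |
| 65 | Miettinen-Nurminen | 70.8% | 2.2% |
| 65 | Agresti-Caffo | 80.5% | 2.9% |

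65 per arm is the best case, in which all 130 patients contribute full information.

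**Step 3: sensitivity to the control rate.** False non-inferiority with Wald, true difference 12 points:
- Control rate 3%: 4.3%, 4.8% and 4.1% at 61, 62 and 65 per arm.
- Control rate 10%: 3.0% at 62 per arm.

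At 62 per arm, Newcombe stays between 2.2% and 2.6% and Miettinen-Nurminen between 2.0% and 2.5% for control rates from 2% to 10%.

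Power also moves with the rate. If the true rate is 4% in both arms, power at 62 per arm is 82.4% (Newcombe) and 81.5% (Miettinen-Nurminen).

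**Step 4: size needed for 80% with a level-holding interval.** At 78 per arm (156 evaluable, 156 / 0.95, about 165 randomised), Newcombe and Miettinen-Nurminen both give 81.9% at 6% v 6%.

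**The case against.** The strongest reply is that nothing has been miscalculated. The 130 follows from a standard textbook formula applied to the stated inputs. That stands: a reader might infer an arithmetic slip or a wrong sample size, and the document does not support that. What fails is the approximation at this event rate, and with it the claim that both properties hold.

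A second reply is that the interval method is commonly left to a statistical analysis plan, which is not at hand. This also stands as far as it goes. A reader might infer that the trial will use Wald and so carries a 3.6% error, but the article says only that a 95% interval will be used. The silence itself is no fault. The point survives because it does not depend on the choice: if the analysis plan names Wald, the published 95% level is off; if it names Newcombe or Miettinen-Nurminen, the published 80% power is.

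Third, a power of about 70% is the lower part of a range. Other intervals give up to about 76% at 62 per arm. With all 130 analysed, Agresti-Caffo reaches 80.5%, though with a 2.9% error at 6% v 18%. The shortfall also rests on the 6% rate and disappears at 4%. These qualifications are correct and limit the size of the claim.

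Finally, it is tempting to show the effect with 3 events in A and 5 in B. At 62 per arm Wald passes this (upper limit 11.9%), while Newcombe and Miettinen-Nurminen allow at most 4 in B. At 61 per arm the Wald limit is 12.04% and all three methods fail it. The example depends on one patient per arm and should carry no weight.

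**Conclusion.** The point holds in conditional form. With about 124 evaluable patients and 6% in both arms, no interval examined delivers both 80% power and a one-sided error of about 2.5%. Wald gives about 82% power with an error of about 3.6% (3.4% to 3.6% over 61 to 65 per arm). Intervals that hold about 2.5% give 69% to 72% for the two usual choices and up to about 76% for others; with 65 per arm the two usual choices give 71% to 75%.

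This rests on 1:1 allocation, equal true rates and the article's own 6%. It does not show that the trial's conclusion will be wrong, nor that Wald is planned. With a level-holding interval the consequence is a higher chance of an inconclusive result; with Wald it is a moderately inflated chance of a false claim of non-inferiority. It is worth correcting before the data are seen, because the correction is cheap and removes a choice that could decide a borderline result.

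**What to change.** In the Statistical analysis section, name the decision interval as Newcombe or Miettinen-Nurminen, two-sided 95%. Because multiple imputation is planned and both intervals are defined on observed 2 × 2 counts, state the form in which the chosen one will be combined across the imputed datasets.

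In the Sample size calculation section, keep the derivation of 130 but say that it comes from the normal approximation. Restate the power for the named interval: about 70% (72% Newcombe, 69% Miettinen-Nurminen) for 124 evaluable patients at 6% in both arms, or 75% and 71% respectively if all 130 are analysed with full information.

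If an analysis plan already names an interval that holds its level, only the power statement needs changing. The cost is two sentences and a less favourable stated power. Enrolment need not change; keeping 80% at a 6% rate with such an interval would instead take about 165 randomised patients.
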